## **5. TREATMENT OF SUBJECTS**

### **5.1 Investigational product / treatment**

#### **Intravenous immunoglobulin product**

Details on Nanogam® 50 mg/ml (RVG 31627) can be found in the SPC and IB.

#### **Placebo**

Details on GPO® (“Gepasteuriseerde Plasma-eiwit Oplossing”, pasteurised plasma protein solution) (RVG16911) can be found in the SPC and IB.

### **5.2 Use of co-intervention**

All medication used during the study will be recorded on the case report form.

## **6. INVESTIGATIONAL MEDICINAL PRODUCT**

### **6.1. Name and description of investigational medicinal product**

The medicinal product under investigation is immunoglobulins (IVIg) (Nanogam®). In this trial the medicinal product is used in a different regiment, which is in a repeated fashion in the same dosage as the first course (2g/kg in 5 days) for patients with severe GBS.

As placebo we will use GPO. This solution contains 40g/l protein, of which 95% is albumin. A summary of findings and information about those medicinal products can be found in the SPC and IB.

### **6.2. Summary of findings from non-clinical studies**

Details on Nanogam and GPO can be found in the SPC.

### **6.3. Summary of findings from clinical studies**

Details on Nanogam and GPO can be found in the SPC.

### **6.4. Summary of known and potential risks and benefits**

Nanogam and GPO are produced by Sanquin Plasma products, Amsterdam. Nanogam and GPO are manufactured from plasma of voluntary, non-remunerated donors. The viral safety of the products have been established by donor selection and screening for HIV1-2, HTLV I/II and hepatitis B and C, by plasma pool screening for HIV, HCV, HBV and Parvo B19 at RNA /DNA level, and by effective inactivation and/or removal of viruses with several physico-chemical methods in the manufacturing process.

The most common adverse effects occur soon after infusion with Nanogam and can include chills, headache, fever, vomiting, allergic reactions, nausea, arthralgia, low blood pressure and moderate low back pain. Side effects are rare during or after infusion of albumin products. Mild reactions such as flush, urticaria, fever, and nausea are usually temporarily and often associated with infusion rate.

### **6.5. Description and justification of route of administration and dosage**

The first (or only) IVIg course in a dosage of 2g/kg in 2-5 days is standard treatment for GBS patients who are unable to walk and still within the first two weeks from onset of weakness, independent of age of the patient or severity of disease. Dose finding studies with IVIg in GBS has never been performed. In some hospitals in the Netherlands neurologists already give a second course of IVIg in patients with severe disease, although the efficacy has never been proven. The second course of IVIg in this trial will be in the same fashion as the first course (0,4 g/kg BW on five consecutive days) because neurologists are familiar with this treatment regiment and it is also used in patients with TRF. Nanogam is manufactured in a 5% solution (50 gram/litre), hence it follows that 0.4 g/kg Nanogam is 8 ml Nanogam/kg BW. Accordingly, 8 ml/kg BW on five consecutive

days of the placebo, GPO, will be administered. GPO and Nanogam will be infused using identical infusion systems.

#### **6.6. Dosages, dosage modifications and method of administration**

Not applicable

#### **6.7. Preparation and labelling of Investigational Medicinal Product**

Every participating hospital owns a buffering stock of IVIg (Nanogam®) and GPO (shelf lives of 3 and 4 years). When a patient is eligible for entering the second RCT phase of this study, the patient will be randomized to get a second IVIg course or placebo. The local pharmacist will prepare the trial medication according to the randomization allocation.

#### **6.8. Drug accountability**

Not applicable

## 7. METHODS

### 7.1. Study parameters/endpoints

#### 7.1.1. Main study endpoint

GBS disability score at 4 weeks after start of first IVIg course. The full range of scores will be considered as an ordinal outcome scale. In analyzing we will use a proportional odds model. (Extent of) improvement on this ordinal scale will be compared between groups.

#### 7.1.2. Secondary study parameters/endpoints

- Percentage of patients that improve:  
at least 1, 2, 3 or 4 points on the GBS disability score at 4, 8, 12 and 26 weeks,  
at least 4, 8 or 12 points on MRC sum score (ranging from 0-60) at 4, 8, 12 and 26 weeks,  
at least 2, 4 or 6 points on ONLS score (ranging from 0-12) at 4, 8, 12 and 26 weeks.
- Percentage of patients needing artificial ventilation.
- Time (number of days) on respirator.
- Time (number of days) on intensive care unit.
- Percentage of patients that die because of GBS.
- Time (number of days) to hospital discharge.
- Percentage of patients with secondary deterioration due to treatment-related fluctuations (TRF).
- Development of complications possibly related to a second IVIg course.
- Serum IgG levels at 5 different time points.

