## SUMMARY

**Rationale:** Guillain-Barré syndrome (GBS) is the most frequent cause of acute neuromuscular weakness in the Western world. GBS patients have a variable prognosis, 20-30% needs mechanical ventilation, 20% is unable to walk after 6 months and 3% dies. Using a simple scoring system it is possible to accurately predict which patient has a poor prognosis. GBS patients with a poor prognosis may benefit from a second course of IVIg.

**Objective:** To determine whether a second IVIg course in GBS patients with a poor prognosis improves functional outcome after 4 weeks. Secondary outcomes include functional outcome after 8, 12 and 26 weeks, mechanical ventilation, length of hospital and ICU admission, occurrence of TRF's, mortality and blood IgG levels.

**Study design:** A double-blind randomized placebo-controlled trial design will be used in selected patients with a poor prognosis. In patients with a good prognosis the study will have an observational design.

**Study population:** GBS patients of 6 years and older, who have an indication for IVIg treatment.

**Intervention:** Patients with a poor prognosis according to the prediction model (mEGOS) will be randomized to receive a second IVIg course or placebo.

**Main study parameters/endpoints:** The main study endpoint is functional outcome on the GBS disability scale 4 weeks after start of the first IVIg course. Other endpoints include functional outcome after 26 weeks.

**Nature and extent of the burden and risks associated with participation, benefit and group relatedness:** The participant will be physically examined at 7 standardized time-points, mostly in combination with the standard patient care. Extra blood and CSF (extra spinal tap is not requested) will be used for trial purposes. An EMG will be performed in the standard clinical work-up. A throat swab will be requested. Serious adverse effects of IVIg are rare (details in SPC). It is anticipated that also in children benefits will outweigh the risks of participating in this treatment trial. Standard treatment in children is the same as in adults, long-term prognosis is better as in adults; however 25% is still not symptom free at a median of 228 days in a large observational study.

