## 1. INTRODUCTION AND RATIONALE

Guillain-Barré syndrome (GBS) is an immune mediated peripheral polyradiculoneuropathy characterized by rapid onset flaccid paresis and sensory disturbances with a very heterogenic distribution in clinical characteristics and in prognosis. Some patients develop mild limb paresis, whereas others develop oculomotor, facial, bulbar, respiratory muscle and limb paralysis and remain bed bound for several months. GBS is the most frequent cause of acute neuromuscular weakness in the Western world[1]. It affects 1.2 persons per 100,000 per year[2]. Intravenous immunoglobulin (IVIg) and plasma exchange (PE) are shown to be effective in patients with GBS[3-6]. These studies primarily assessed the proportion of patients that improved 4 weeks after onset of this treatment. Nowadays, IVIg (2 g/kg in 2-5 days) has become standard treatment for patients with GBS who are unable to walk unaided and still within the first 2 weeks from onset of weakness[4, 7, 8]. The outcome of GBS after 6 or 12 months however has not, or only marginally been improved[1, 6]. Approximately 20% are still disabled after 6 months, mechanical ventilation is needed in 20-30% and 3%-10% of the patients die. Patients with severe GBS and poor prognosis may need additional or more aggressive therapy to recover. Careful selection of patients eligible for extra therapy is important, because extra treatment entail added complication risk and costs. Multiple clinical, electrophysiology, serological and laboratory factors have been identified as predictors for poor outcome. These include older age[9-11], rapid disease progression[11], disability grade[10, 12, 13], preceding diarrhea/Campylobacter jejuni serology[9, 10, 12], absence of antecedent upper respiratory tract infection[12, 13], axonal EMG[12, 13] and anti-GM1 antibodies[14, 15]. A recent study showed that the prognosis of individual GBS patients can accurately be predicted based on three simple clinical factors that can easily be obtained early during the course of disease[10]. The selection of patients for the RCT phase of this SID-GBS study is based on this prognostic model.

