### Secondary objectives

To investigate whether:

- a second IVIg dosage in GBS patients with a poor prognosis improve functional outcome or muscle strength after 8, 12 and 26 weeks.
- a second IVIg dosage in GBS patients with a poor prognosis lowers the percentage of patients needing artificial ventilation, lower the time (number of days) on respirator or time on the intensive care.
- a second IVIg dosage in GBS patients with a poor prognosis reduces the time to hospital discharge.
- a second IVIg dosage in GBS patients with a poor prognosis reduce the chance of secondary deterioration due to treatment-related fluctuations (TRF†).
- patients treated with a second IVIg dosage develop more complications possibly related to the second IVIg treatment.
- a second IVIg dosage in GBS patients with a poor prognosis lowers the percentage of patients that die because of GBS.
- the serum IgG increase after the first IVIg dosage is lower in patients with a poor prognosis.
- serum IgG increases further (and to what extent) after administration of a second IVIg dosage.

† A TRF is defined as (1) improvement in the GBS disability score of at least one grade or improvement in the MRC sum score (0-60) of more than 5 points after completion of therapy, followed by a worsening in the GBS disability score of at least one grade or a decrease in the MRC sumscore of more than 5 points within the first months after onset of disease or (2) stabilization of the clinical course for more than 1 week after completion of therapy, followed by a worsening of at least one grade of the GBS disability score or more than 5 points on the MRC sumscore.

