#### **7.7. Premature termination of the study**

Severe complications attributable to IVIg are rare. Yet, clinical evidence of an association between thrombo-embolic complications (myocardial infarction, stroke, lung embolism, deep venous thrombosis) and IVIg treatment exists. This association is probably attributable to the relative increase in blood viscosity because of the high influx of immunoglobulins. It is imaginable that a second dosage of IVIg in a short period further increases the chance of developing such a severe complication, especially in patients with pre-existing risk factors of thrombo-embolic complications (older age, hypertension, diabetes mellitus, history of vascular disease or thrombo-embolic illnesses, patients with acquired or inborn pre-thrombotic disease, patients with long term immobilization, deep hypovolemic state and patients who have illnesses which cause increased viscosity of the blood). Extra precautions will be taken in patients with pre-existing risk factors for thrombo-embolic complications and patients with kidney function disturbances. When

significantly more severe complications occur most likely attributable to the second IVIg dosage the study will be prematurely terminated.

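### The only mortality endpoint counts deaths because of GBS, so a death attributed to the second IVIg course is left out of the mortality comparison

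*Protocol*

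**What the plan says.** Section 7.1.2 lists one endpoint on death: "Percentage of patients that die because of GBS". The matching objective in Section 2 asks whether "a second IVIg dosage in GBS patients with a poor prognosis lowers the percentage of patients that die because of GBS". The restriction stands in both places, so it is not a slip in one of them.

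Two other parts of the protocol treat death without regard to cause. The Summary names among the secondary outcomes "occurrence of TRF's, mortality and blood IgG levels". Table 3 in Appendix A makes death grade 6 of the GBS disability score, and Section 7.1.1 analyses the full range of that score at 4 weeks.

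On harm, Section 7.7 states that "clinical evidence of an association between thrombo-embolic complications (myocardial infarction, stroke, lung embolism, deep venous thrombosis) and IVIg treatment exists", and adds: "It is imaginable that a second dosage of IVIg in a short period further increases the chance of developing such a severe complication". The rationale in Section 1 says that impaired mobility may also make neurologic patients prone to thrombo-embolism. Section 7.2 allows the blind to be broken at a serious adverse event, depending on its severity and how likely a relation to IVIg is; the treating neurologist then knows the arm.

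Section 7.1.2 lists no comparison of death from any cause over the six months of follow-up.

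**The concern.** The endpoint sorts deaths by presumed cause after randomisation, and the cause that it excludes is one the protocol itself connects with the treatment under test. Deaths truly caused by the second course can occur only in the IVIg arm, so leaving them out affects that arm alone.

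Attribution is also open to judgement. Lung embolism in a paralysed patient can be put down to immobility, and so to GBS, or to the infusion. If the treating neurologist has been unblinded, the same event could be ascribed to disease under placebo and to treatment under IVIg.

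At stake is what the trial report says about survival. A mortality line that omits treatment-attributed deaths may look neutral or favourable when deaths from any cause are equal or higher under IVIg. The protocol also leaves unclear which quantity it means to compare, since the Summary and the endpoint list describe different ones.

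**Working it through.** **1. The plan's own figures.** Section 4.4 takes 60% of 290 = 174 patients, half of whom have a poor prognosis: 0.50 × 174 = 87, or about 44 per arm. This reproduces. The protocol states no sample size or power for mortality.

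**2. Expected deaths per arm.** Section 1 gives "3%-10% of the patients die"; the Summary gives the lower end, "20% is unable to walk after 6 months and 3% dies". Expected deaths = arm size × death rate:

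- 44 × 0.03 = 1.3
- 44 × 0.10 = 4.4

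These rates are for GBS patients in general. Section 1 puts 48% of patients at mEGOS 6 or higher. If every death fell in that group (an assumption, and an upper bound):

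- 44 × 0.03 / 0.48 = 2.75
- 44 × 0.10 / 0.48 = 9.2

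**3. Equal all-cause mortality, some deaths attributed to IVIg.** Let the all-cause rate be *q* in both arms, and let a fraction *f* of IVIg-arm deaths be attributed to treatment. The endpoint then compares *q*(1 − *f*) with *q*, an apparent relative risk of 1 − *f*. The documents give no value for *f*; 25% and 50% are assumptions.

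| All-cause rate, both arms | *f* | Endpoint, IVIg v placebo | Apparent relative risk |
|---|---|---|---|
| 3% | 25% | 2.25% v 3% | 0.75 |
| 3% | 50% | 1.5% v 3% | 0.50 |
| 10% | 25% | 7.5% v 10% | 0.75 |
| 10% | 50% | 5% v 10% | 0.50 |

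The true all-cause relative risk is 1 in every row. At 10% and *f* = 50%, the expected counts on the endpoint are 2.2 v 4.4.

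**4. Treatment deaths added to an unchanged GBS risk.** Let GBS deaths be 10% in both arms, and let 5% of IVIg patients die from treatment, independently and first (assumptions).

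- Endpoint: 0.10 × (1 − 0.05) = 9.5% v 10%
- Death from any cause: 1 − 0.90 × 0.95 = 14.5% v 10%

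The endpoint shows almost no difference (44 × 0.005 = 0.2 of a death) while all-cause mortality is 4.5 percentage points higher. Here the effect is to hide harm, not to create a visible benefit.

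**5. Could this produce a significant result?** Hardly. Fisher's exact test gives p = 0.68 for 2/44 v 4/44 and p = 0.12 for 0/44 v 4/44. Power to detect 10% v 5% with 44 per arm is about 14%.

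**The case against.** The strongest reply is that the trial separates disease deaths from treatment harms and measures both. A death by week 4 is the worst category of the primary outcome, whatever its cause. Section 7.1.2 also compares improvement on the disability score at 8, 12 and 26 weeks, and a patient who has died cannot improve. A fatal embolism is a serious adverse event under Section 8.2, falls under the complications endpoint, and comes before the data safety monitoring board. All of this stands: the deaths are not lost. But the primary analysis counts grade 6 at 4 weeks only, and no listed endpoint compares death itself, from any cause, to the end of follow-up.

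A second reply is that a thrombo-embolic death may well be classed as due to GBS, because Section 1 links that complication to immobility. This also stands, and it rules out saying that every such death is excluded. It does not rescue the endpoint, because it shows that the count depends on judgement.

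A third is that the sizes rest on assumptions. The protocol calls thrombo-embolic complications rare and calls a further increase after a second dose only conceivable. Section 4.3 excludes severe cardiovascular disease and malignancy, and deaths before randomisation at about day 7 do not count in either arm. That is fair, and it limits the claim about size.

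Finally, rules for assigning cause of death may be in a statistical analysis plan that is not shown, so their absence is not held against the protocol. The cause restriction itself is fixed in the protocol.

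**Conclusion.** The point holds in a limited form. The only mortality endpoint is cause-specific, it disagrees with the unqualified mortality in the Summary, and it omits any death attributed to the second course. Because attribution can differ by arm, the comparison can mask harm or move the point estimate towards IVIg.

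Two stronger readings are tempting and not supported. A reader might infer that IVIg would be shown to save lives when it does not. That needs differential attribution or competing causes on a scale the documents do not give; with purely additional treatment deaths the endpoint stays close to null, and with so few events a significant false benefit is unlikely. A reader might also infer that one or two deaths would reverse a real finding. With these counts either direction is compatible with chance, so what changes is the reported estimate, not a firm conclusion.

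The size rests on the protocol's 3% to 10% mortality applied to 44 per arm: about 1.3 to 4.4 deaths per arm, up to about 2.8 to 9.2 if all deaths fall in the randomised prognostic group. The apparent relative risks of 0.50 to 0.75 depend wholly on the assumed 25% to 50% attribution. This is worth correcting, but it does not threaten the primary analysis.

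**What to change.** In Sections 2 and 7.1.2, define the endpoint as death from any cause by 26 weeks, compared by randomised arm. Keep deaths attributed to GBS as a descriptive breakdown only. This matches the Summary and the disability scale.

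The cost is small: two changes of wording, no extra patients and no extra visits. One step is needed. Section 3 discharges patients who have fully recovered at 3 months from further follow-up, so their vital status at 26 weeks must be confirmed. Blinded adjudication of cause would be an added procedure, and this fix does not need it, because the compared endpoint no longer depends on cause.

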## 7.2. Randomization, blinding and treatment allocation

All GBS patients in need of IVIg treatment are potentially eligible for this study. All participants will be evaluated after first IVIg treatment and scored following the modified EGOS model. Patients with a poor prognosis according to this model will be randomized to receive a second IVIg dosage or placebo. For that a randomization website is used (see the signed agreement with CTCM). A computer-generated list of random assignments (block randomization per site) is prepared in advance. When a PI registers a patient to the website a box number is generated and an email with this box number will be sent automatically to the local pharmacist (and the central pharmacy of the Erasmus MC, the coordinating investigator, the co-investigator, Sanquin and the registering PI). The box number corresponds to the randomization list and the local pharmacist will prepare the study medication according to the randomization allocation. The PI will prescribe the trial medication in the same dosage as the first treatment (2 g/kg administered in 5 consecutive days). The coordinating investigator, the co-investigator, the PI and the trial coordinator of Sanquin as well as the patient will be blinded to the treatment.

Blinding will be broken in case of a Serious Adverse Event considering the severity of the adverse event and the likeliness of a relation to IVIg treatment after conference between the investigators, Sanquin and the treating neurologist. The treating neurologist will then be unblinded and is responsible for treatment of the possible side effects of the IVIg treatment.

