#### **7.6. Follow-up of subjects withdrawn from treatment**

For all subjects who are prematurely withdrawn from treatment, the reason will be documented carefully. The patients who had at least one dose of study medication will at least be included in the safety evaluation.

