### **8.2. Adverse and serious adverse events (SAE)**

Adverse events are defined as any undesirable experience occurring to a subject during a clinical trial, whether or not considered related to the investigational drug. All adverse events reported spontaneously by the subject or observed by the investigator or his staff will be recorded.

A serious adverse event is any untoward medical occurrence or effect that at any dose;

- results in death
- is life threatening (at the time of the event)
- requires hospitalization or prolongation of existing inpatients' hospitalization\*
- results in persistent or significant disability or incapacity
- is a congenital anomaly or birth defect
- is a new event of the trial likely to affect the safety of the subjects, such as an unexpected outcome of an adverse reaction, lack of efficacy of an IMP used for the treatment of a life threatening disease, major safety finding from a newly completed animal study, etc

*\*all patients in this trial are hospitalized, this is not considered to be a serious adverse event.*

All SAE's will be reported to the accredited METC that approved the protocol, according to the requirement of that METC.

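### The only listed endpoint for treatment harm counts complications by their possible link to the second IVIg course, which placebo patients do not receive, instead of all events by randomised arm

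*Protocol*

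**What the plan says.** Section 7.1.2 gives the harm endpoint as "Development of complications possibly related to a second IVIg course". The secondary objectives in section 2 put the between-arm question with the same filter: whether "patients treated with a second IVIg dosage develop more complications possibly related to the second IVIg treatment". The only other listed item close to safety is "Percentage of patients that die because of GBS", which is also defined by cause, although the Summary names mortality without that limit ("length of hospital and ICU admission, occurrence of TRF's, mortality and blood IgG levels").

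Data collection is wider than the endpoint. Section 8.2 defines an adverse event as one counted "whether or not considered related to the investigational drug" and adds that "All adverse events reported spontaneously by the subject or observed by the investigator or his staff will be recorded". Section 7.6 says "The patients who had at least one dose of study medication will at least be included in the safety evaluation", but names no measure or comparison. Section 8.4 provides for a yearly safety analysis, and section 8.6 has the DSMB look at safety data every six months. Neither these sections nor section 9 makes a comparison of all adverse events or all SAEs between the arms an endpoint.

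On blinding, section 7.2 keeps the patient, the site investigator and the coordinating investigators blinded. For an SAE, the blind is broken after a conference that considers how severe the event is and how likely a link to IVIg is. Then "The treating neurologist will then be unblinded".

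**The concern.** A randomised comparison of harm is cleanest when an event counts in the same way in both arms, whatever anyone believes caused it. Here the definition of the event refers to the exposure under test.

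The protocol's own design makes that attribution hard. Section 4.2 B requires a full first course of 2 g/kg before randomisation, and section 3 starts trial medication within 24 hours of an assessment on day 7 (at the latest day 8 or 9). Section 1 names impaired mobility, and section 7.7 long-term immobilisation, as thrombo-embolic risks. A thrombosis or a renal event could come from the first course, the trial infusion or the disease.

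Excess thrombo-embolic harm is one of the protocol's stated reasons for not giving every patient a second course. With 44 patients per arm, a few events left out or kept in can change the reading of the safety result.

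**Working it through.** The protocol gives no event rate, attribution rate or power for this endpoint, so there is no planned figure to reproduce. The check is a reading of the safety sections, then an illustration with assumed rates.

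**Reading**

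- Collection (8.2): all adverse events, related or not.
- Endpoint and objective (7.1.2, 2): only complications with a possible link to the second course.
- Placebo arm (3, 6.1): plasma protein solution, so no second IVIg course as trial treatment. There is one exception. Under section 7.2, a treatment-related fluctuation during trial medication leads to open IVIg, so a placebo patient may get a second course after all and an IVIg patient a further one. That makes the reference to a second course less clear still.

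**Illustration (all rates assumed; 44 per arm from section 4.4)**

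Let b be the background events expected in each arm, d the excess caused by the second course, and r_b and r_d the shares of each that are judged possibly related. If the judgement works alike in both arms:

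- placebo count = b × r_b
- IVIg count = b × r_b + d × r_d
- counted difference = d × r_d

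Take b = 4 and d = 4, so the truth is 8 against 4.

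| r_b | r_d | IVIg | Placebo | Difference |
|---|---|---|---|---|
| 1 | 1 | 8 | 4 | 4 |
| 0.5 | 0.5 | 4 | 2 | 2 |
| 0.5 | 1 | 6 | 2 | 4 |

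The second row halves the absolute difference and leaves the ratio at 2:1. The third keeps the difference and raises the ratio to 3:1.

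The same holds for power, from the two-sided 5% normal approximation Φ[(Δ − 1.96 × SE0)/SE1], where SE0 uses the pooled rate and SE1 the separate rates. Take true rates of 30% and 45%.

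- All events: Δ = 0.15, SE0 = √(2 × 0.375 × 0.625/44) = 0.1032, SE1 = √((0.21 + 0.2475)/44) = 0.1020, power about 30%.
- Half of all events kept (15% against 22.5%): Δ = 0.075, SE0 = 0.0832, SE1 = 0.0828, power about 14%.
- Half of the background and all of the excess kept (15% against 30%): Δ = 0.15, SE0 = √(2 × 0.225 × 0.775/44) = 0.0890, SE1 = √((0.1275 + 0.21)/44) = 0.0876, power about 39%.

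If the judgement differs by arm, the comparison can move either way. With a true rate of 30% in both arms:

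- shares of 30% (placebo) and 50% (IVIg): 0.30 × 0.30 = 9% against 0.30 × 0.50 = 15%, a false excess of 6 points
- the reverse: 15% against 9%, a false deficit of 6 points

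The counted result thus depends on the attribution shares as well as on the events, and the protocol gives no means of knowing those shares.

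**The case against.** **Blinding.** The assessors do not know which infusion was given, so in practice they judge a link to the trial infusion, in the same way in both arms. Difficulty in separating the first course, the infusion and the disease is then also shared. This stands: it limits differential attribution. It does not stop real events from being dropped.

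**Unblinding.** A reader might infer that relatedness is judged once the allocation is known, which would produce a false excess in the IVIg arm. The protocol does not support that. In section 7.2 the likelihood of a link is weighed first and is an input to the decision to unblind, and only the treating neurologist is named as then learning the allocation. A later revision by someone unblinded is conceivable, but the text does not provide for it.

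**Another reading of the phrase.** It may mean types of complication known with IVIg (thrombo-embolic, renal, anaphylactic; sections 4.3 B, 7.7 and 10.4), counted in both arms. That is possible, and it is close to the remedy below. The wording does not say so, however, and the objective repeats the link to the second treatment.

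**A filter can help.** A low threshold that removes only background events keeps the difference and reduces noise, as the 39% case shows. This also stands, and it is why no direction is claimed.

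**Other safety review.** All events are recorded, the DSMB sees safety data, death is grade 6 of the primary scale, and a statistical analysis plan may tabulate all events by arm. A reader should therefore not infer that unrelated events go uncollected or unseen. The point is limited to what the protocol declares as its objective and endpoint.

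**Conclusion.** The point holds as a weakness in how the safety endpoint is defined. The one listed measure of treatment harm, and the objective behind it, rest on attribution to a course that placebo patients do not receive as trial treatment. The recent first course and immobility make that attribution unreliable. Real events can be lost and the comparison between arms can be distorted.

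The size and direction of the effect are unknown. The illustrations run from a halved difference to an unchanged one with a higher ratio, and all of their rates are assumed. Bias through unblinding is a residual risk, not a demonstrated one. The conclusion rests on the wording of sections 2, 7.1.2, 7.2 and 8.2, and on no event rate. Changing the definition is a cheap improvement worth making.

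**What to change.** Reword the harm objective in section 2 and the endpoint in section 7.1.2 so that the safety endpoint is:

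- all adverse events, all SAEs, and the complication types already named in the protocol (thrombo-embolic, renal, anaphylactic)
- with onset from the start of trial medication to week 26 or the end of follow-up, since section 3 releases patients who are fully recovered at 3 months
- compared by randomised arm, irrespective of relatedness

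Keep the relatedness judgement, made under the blind, as a supplementary table. Deaths from any cause are then covered, because section 8.2 counts fatal events as SAEs.

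The cost is wording in two sections. No new data are needed, and no treatment or clinical rule changes. The drawback is that complications of the disease itself will be counted and will add some background noise in both arms. The supplementary table lets readers see how much of the total that is.
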